## Rationale for the study

Combination therapy and a shorter course of effective medication in the treatment of diseases have been shown to improve outcomes in human immunodeficiency virus AID (HIV-AID) infection, tuberculosis, acute pyogenic infections and epilepsy [12–15]. If the critical time for severe malaria treatment is the first 24 h of illness, aggressive therapy targeted during this time using a synergistic combination of intravenous artesunate-quinine has a potential for rapid parasite clearance and reduce morbidity and mortality. This trial is feasible because of the long-standing biosafety profiles of artesunate and quinine. We are optimistic that the results of this trial may stimulate the interest of pharmaceutical companies in the development of newer formulations of intravenous antimalarial combination therapies; this could improve the availability and administration of treatment within the first 24 h and consequently improve the health outcomes in patients diagnosed with cerebral malaria.

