### Interventions

#### Intervention description {11a}

The experimental arm will receive a combination of intravenous quinine plus artesunate. A clinical pharmacologist (unblinded) will deliver the allocated treatment to the clinician (blinded) for administration.

This group will receive a combination of intravenous quinine plus artesunate. The quinine will be given at a loading dose of 20 mg/kg and subsequently 10 mg/kg 8 h for 72 h. However, if the patient remains unconscious, the dose will be reduced to 7.5 mg/kg 8 hourly until he/she regains consciousness. In parallel, intravenous artesunate at 3 mg/kg if weight is less than 20 kg or 2.4 mg/kg if weight is greater than 20 kg at 0, 12, and 24 h and subsequently a daily dose of 1.2 mg/kg/day until conscious.

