#### All the groups

The two groups will receive enteral artemisinin-based combination therapy (ACT) as soon as they regain consciousness and can tolerate the full course of oral ACT in line with WHO recommendation.

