#### Criteria for discontinuing or modifying allocated interventions {11b}

Participants who regained full recovery after initial treatment.Participants who also wish to exit after due counselling.Participants with intractable hypoglycaemia despite maintenance at 12.5% glucose.Participants with dysrhythmias will be unblinded.Participants who develop commodities of severe malaria that could confound the measurable outcomes such as uraemic encephalopathy.Participant with a new disease besides cerebral malaria or updated clinical history related to exclusion criteria.

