#### Secondary outcomes

Number of patients that regained full consciousness as measured by GCS/MGCS of > 11 for children > 5 years or Blantyre Coma Scale of > 3 in children < 5 years at 12 and 24 h post-randomization.Number of patients with asexual form of malaria parasite present or absent at 12 and 24 h post-randomization.Number of patients that achieved fever defervescence (attainment and sustenance of axillary temperature of < 37.5 °C) at 12 and 24 h post-randomization.Parasite density at 12 and 24 h post-randomization.Number of patients with neurologic deficits at the fourth week (day 29) post-intervention in each of the arms. Neurology deficit is defined as the presence of impaired cognitive, motor or cranial nerve palsy and or persistence of convulsions.Time to convert to a full dose of enteral artemisinin-based combination therapy.The side effect profile (adverse events and serious adverse events) of medication in each arm of study: (i) solicited side effects include hypoglycaemia, arrhythmia, thrombocytopenia, tinnitus and anaemia; (ii) unsolicited adverse events as reported by patients post-randomization; (iii) random plasma glucose will be measured 6 hourly until 48 h after parasite clearance. Hypoglycaemia will be corrected with 2-4 ml/kg of 10% D/W and maintenance with glucose infusion at 6–8 mg/kg/min until euglycaemic; (iv) electrocardiography will be recorded before the administration of anti-malaria and 4 h after an intervention. The QT and RR will be measured by software and checked manually. Bazett’s formula will be used to correct the QT interval (QTc = QT/RR**0.5). Prolonged QT interval managed as per hospital protocol; (v) haematocrit, serum ferritin, platelet count and erythrocyte sedimentation rate will be monitored at baseline and 24 h and 48 h post-randomization.Plasma levels of inflammatory markers including C reactive protein, procalcitonin, lactate dehydrogenase and interleukin 6 at baseline, 24 h, and 48 h. Inflammatory markers and cytokine are included to assess a possible ‘cytokine storm’ in the course of parasite clearance.

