**Assessments**							
Electrocardiograhy	x	x	x	x	x		
*Survival*		x	x	x	x		
*Regained consciousness*		x	X				
*Parasitaemia*		X	X			.	
*Defervescence*		X	X				
*Adverse events*	x	x	x	x	x	x	x
*Haematological indices*	x		x	x			
*Inflammatory markers*	x		x	x			
*Glucose monitoring*	x	x	x	x	x	x	

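### 6-hourly glucose testing stops 48 h after parasite clearance, so the intensive search for hypoglycaemia can differ in length by arm; the bias is probably small and cheap to remove

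*Protocol article*

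**What the plan says.** All references are to the protocol article.

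- **Outcomes {12}, Secondary outcomes.** Hypoglycaemia heads the solicited side effects, which are to be profiled in each arm. The testing rule is that "random plasma glucose will be measured 6 hourly until 48 h after parasite clearance". Parasitaemia is recorded as "asexual form of malaria parasite present or absent at 12 and 24 h post-randomization".
- **Participant timeline {13}.** Glucose monitoring is marked at 0, 12, 24, 48 and 72 h and at 29 days. Parasitaemia is marked at 12 and 24 h only.
- **Rationale for the study.** The combination "has a potential for rapid parasite clearance". Parasite clearance is also a specific objective.
- **Intervention description {11a}.** After the loading dose, quinine is given at "subsequently 10 mg/kg 8 h for 72 h". If the child remains unconscious, "the dose will be reduced to 7.5 mg/kg 8 hourly until he/she regains consciousness".
- **All the groups.** Both arms move to oral treatment "as soon as they regain consciousness and can tolerate the full course of oral ACT".
- **Criteria for discontinuing or modifying {11b}.** One criterion is "Participants who regained full recovery after initial treatment".
- **Control arm.** Controls receive intravenous 10% dextrose where the other arm receives quinine.
- **Statistical methods {20a}.** Categorical outcomes are compared by chi-squared or Fisher's exact test, with risk differences and risk ratios. No common glucose window is stated.

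**The concern.** The chance of finding a low glucose depends on how often and how long one looks. Here the stopping point is set by a post-randomisation outcome that the experimental treatment is expected to change. If the dual arm clears faster, as the trial hopes, its early clearers have fewer 6-hourly readings. That alone lowers detected hypoglycaemia in the arm given the extra drug, and a plain comparison of proportions does not allow for it.

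The stop is also not tied to drug exposure. A child whose smear is clear at 12 h can leave 6-hourly testing while quinine is still being given. What is at stake is a safety comparison of the added drug, not the primary outcome.

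**Working it through.** **1. When testing stops.** Stop time = clearance time + 48 h. The two scheduled smears give:

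- clear at 12 h: 12 + 48 = 60 h
- clear at 24 h: 24 + 48 = 72 h

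**2. Post-baseline readings within 0-72 h**, counting the 72 h mark in the timeline:

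- clear at 12 h: 6, 12, ..., 60 h (10 readings) plus 72 h = 11
- clear at 24 h: 6, 12, ..., 72 h = 12

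The only reading missed is the one at 66 h.

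**3. Effect on detection.** The protocol gives no hypoglycaemia rate, so assume a constant chance p per reading of 2%, with range 1-3%. Detected risk with n readings is 1 − (1 − p)^n, and the loss from one missing reading is p(1 − p)^11. If 20 percentage points more dual-arm children clear at 12 h rather than 24 h (also an assumption), the arm difference from testing length alone is 0.20 × that loss.

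| p | 11 readings | 12 readings | loss (points) | × 0.20 (points) |
|---|---|---|---|---|
| 1% | 10.47% | 11.36% | 0.895 | 0.18 |
| 2% | 19.93% | 21.53% | 1.601 | 0.32 |
| 3% | 28.47% | 30.62% | 2.146 | 0.43 |

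At 2%, with all controls clear at 24 h, the risk ratio is (21.53 − 0.32)/21.53 = 0.985. Clearance shifts of 10 to 40 points with p from 1% to 3% give 0.09 to 0.86 points.

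**4. If risk falls with time.** Let the risk per reading halve every 12 to 24 h, scaled so that the 12-reading total is unchanged. The 20-point shift then gives 0.04 (12 h) to 0.12 (24 h) points at 2%, and 0.02 to 0.16 points over 1-3%.

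**5. Scale.** At 20% risk with 235 per arm, the standard error of the arm difference is √(2 × 0.2 × 0.8/235) = 0.037, or 3.7 points. The base case is 0.32/3.7 = 0.09 of a standard error. If every dual-arm child cleared at 12 h and every control at 24 h, the figure at 2% would be 1.60 points, or 0.43 of a standard error.

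**6. Quinine exposure.** Taking 8-hourly doses from 0 h, the times are 0, 8, ..., 56, 64 h. The 64 h dose falls after the 60 h stop. The next scheduled glucose is at 72 h, which is 72 − 64 = 8 h after that dose.

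**7. What is already common to all.** With the first smear after enrolment at 12 h, the scheduled rule cannot end 6-hourly testing before 60 h. Every child who survives and stays on study therefore has the same 60/6 = 10 post-baseline readings over 0-60 h.

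**The case against.** The case for leaving the rule alone is strong in several respects.

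- **It is a bedside safety rule.** Watching longer while parasites persist is sensible, the rule is the same in both arms, and it is applied under blinding. That stands, and is why the extended testing of late clearers should be kept.
- **The quantified effect is negligible.** The base case is under one tenth of a standard error and would change no conclusion about hypoglycaemia. That stands.
- **A common window already exists.** Complete 6-hourly data to 60 h can be compared with no new sampling, and a window for an adverse event is often left to the analysis plan. The first part stands and supplies the simplest fix. The second is only a partial answer, because the outcome-dependent stop is a rule the protocol itself states.
- **The quinine gap is narrow.** It needs a child clear at 12 h who is still on intravenous quinine at 64 h, because still unconscious or unable to take oral treatment, and who has not been stopped for full recovery. If unconscious, that child is on the reduced dose. The gap is 8 h, and adverse events are recorded throughout. That stands.

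A reader might infer that the rule hides quinine-induced hypoglycaemia, or clearly favours the dual arm. The documents do not support this. Testing does not cease at 60 h, since 72 h and day 29 are marked for all. Dextrose may itself lower hypoglycaemia in controls, so the net direction of the comparison is uncertain. A reader might also infer a larger bias from children who clear late and are tested for longer. With no smear scheduled after 24 h, nothing in the article fixes when their 48 h clock starts, so that part cannot be sized.

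**Conclusion.** The point holds as a minor, optional improvement. The protocol makes the length of intensive glucose testing depend on an outcome that treatment may change, and for some children it ends before the planned quinine course. Within 0-72 h the distortion is about 0.3 percentage points or less at an assumed 2% per reading and a 20-point clearance shift, against a standard error of 3.7 points, and it is smaller if hypoglycaemia is concentrated early. These figures rest on assumed hypoglycaemia rates and clearance shifts, on the 72 h timeline reading being taken, and on clearance being read at the scheduled 12 and 24 h smears. Clearance after 24 h remains unquantified.

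**What to change.** 1. **Analysis.** Compare hypoglycaemia between arms over one fixed window common to all children, and list later episodes separately by arm. The 0-60 h window is already complete under the present schedule; use 0-72 h if testing is extended as below. Either choice removes the dependence on clearance, including the extra testing of late clearers.
2. **Monitoring.** In both arms, measure glucose 6-hourly until at least 72 h after randomisation, or until 48 h after clearance if that is later. This covers the planned quinine course and keeps the protection for late clearers. Align the glucose row of the timeline with it.

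**Cost.** The first change is wording only. The second adds one reading (66 h) for children clear at 12 h and none for those clear at 24 h or later. That is at most 470 × 1 = 470 readings in the trial, or 0.20 × 470 = 94 if 20% clear at 12 h (assumption). Later episodes fall outside the main comparison, and follow-up cut short by death is not equalised. The clock for clearance after 24 h still has no scheduled smear, but the arm comparison would no longer depend on it.

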### Participant timeline {13} [18]

**Table Tabb:** 

	Study period						
	Timeline						
**Event/activities**	**0 h**	**12 h**	**24 h**	**48 h**	**72 h**	**29 days**	***t***_***x***_
**Enrolment**							
Eligibility screen	x						
Informed consent	x						
*Anthropometry measurement*	x						
*Clinical history and detailed CNS examination*	x					X	
Allocation	X						
**Interventions**							
*Artesunate + quinine—8 hourly*	x	x	x	x	x	…	
*Artesunate—12 hourly*	x	x	x	x	x	…	
**Assessments**							
Electrocardiograhy	x	x	x	x	x		
*Survival*		x	x	x	x		
*Regained consciousness*		x	X				
*Parasitaemia*		X	X			.	
*Defervescence*		X	X				
*Adverse events*	x	x	x	x	x	x	x
*Haematological indices*	x		x	x			
*Inflammatory markers*	x		x	x			
*Glucose monitoring*	x	x	x	x	x	x	

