### Statistical methods for primary and secondary outcomes {20a}

Data from this study will be analysed using the GraphPad Prism 9 (GraphPad Software, [name]). The appropriate descriptive statistics will be used to present the socio-demographic characteristics of study participants. The comparison of categorical outcomes between the arms will be analysed using the chi-squared or Fisher’s exact tests, as appropriate, and presented as risk differences, risk ratios, and 95% confidence intervals. Kaplan-Meier analysis and Cox regression models will be used to compare the recovery of consciousness, defervescence, and survival.

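### Time to recovery of consciousness is an objective with a planned Kaplan-Meier/Cox analysis, but consciousness and fever are scheduled only at 12 and 24 h, so later recovery is not captured

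*Protocol article*

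**What the plan says.** All places are in the protocol article.

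- **Specific objectives:** the time children take to regain consciousness is listed as an objective. Defervescence is listed without a time element.
- **Secondary outcomes:** consciousness is a count, "Number of patients that regained full consciousness as measured by GCS/MGCS of > 11 for children > 5 years", with the younger group's threshold and the times given as "Blantyre Coma Scale of > 3 in children < 5 years at 12 and 24 h post-randomization". Defervescence is also a count, defined as "attainment and sustenance of axillary temperature of < 37.5 °C) at 12 and 24 h post-randomization". No time-to-recovery outcome is defined.
- **Participant timeline {13}, Assessments:** the rows "Regained consciousness" and "Defervescence" are marked at 12 and 24 h and nowhere else. Survival, electrocardiography and glucose are marked through 72 h.
- **Intervention description {11a}:** after the 24 h dose, artesunate continues as "subsequently a daily dose of 1.2 mg/kg/day until conscious". The control-arm section has the same rule, and the quinine text provides for a child who stays unconscious.
- **Statistical methods {20a}:** "Kaplan-Meier analysis and Cox regression models will be used to compare the recovery of consciousness, defervescence, and survival".

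**The concern.** The objective and the analysis treat recovery as a time. The outcome definition and the schedule treat it as two yes/no readings, the last at 24 h. The treatment rules expect some children to be unconscious beyond that point.

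These children, with the longest comas, would contribute no recovery event. A difference present at 24 h and gone by 48 h could not be told from one that lasts. An analysis plan written later can refine the method but cannot restore readings that were never recorded. The primary outcome, survival at 48 h, is not affected.

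**Working it through.** **1. No stated figure to reproduce for this endpoint.** The protocol gives no median, hazard ratio or power for recovery. Its 470 belongs to the primary comparison and is broadly reproducible. For 23.0% v 12.5%, two-sided 0.05 and 80% power, the pooled formula n = [1.96√(2p̄q̄) + 0.842√(p₁q₁ + p₂q₂)]²/δ², with p̄ = 0.1775 and δ = 0.105, gives 207 per arm. Then 207/0.9 = 230 per arm, or 460 in total, close to 470. It serves here only as the number of children: 470 × 0.9 = 423, or 211.5 per arm.

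**2. What two readings can show.** Each child falls into one of three groups: recovered by 12 h, recovered between 12 and 24 h, or not recovered by 24 h. The curve has at most two steps, and each recovery is dated up to 12 h late. If fewer than half of an arm recover by 24 h, its median does not exist in the data. For fever, a child below the threshold at both 12 and 24 h shows a sustained response. A child first below it at 24 h has no later scheduled reading.

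**3. How many children are unresolved at 24 h.** Assume exponential recovery with median m and no deaths. The share unrecovered at 24 h is 0.5^(24/m):

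| Assumed median | 12 h | 18 h | 24 h | 36 h | 48 h |
|---|---|---|---|---|---|
| Unrecovered at 24 h | 25% | 40% | 50% | 63% | 71% |

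**4. Recoveries lost by stopping at 24 h.** Assume a hazard ratio of 1.3 for recovery. Events by time T are the sum over arms of n(1 − exp(−λT)), and approximate power is Φ(½√D · ln 1.3 − 1.96).

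| Control median | Events by 24 h v 72 h | Share after 24 h | Power, 24 h v 72 h |
|---|---|---|---|
| 18 h | 275 v 404 | 1 − 275/404 = 32% | 59% v 75% |
| 24 h | 231 v 382 | 1 − 231/382 = 40% | 51% v 73% |
| 36 h | 174 v 335 | 1 − 174/335 = 48% | 41% v 67% |

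**5. Deaths.** Step 4 ignores them. If the 23.0% and 12.5% in the sample-size section are deaths before recovery, at most 211.5 × 0.77 + 211.5 × 0.875 ≈ 348 children can recover. The 382 and 404 above exceed that ceiling. At 348 events the power formula gives Φ(½√348 × 0.262 − 1.96) ≈ 69%, so 73% and 75% are out of reach. Scaling the arms to 162.9 and 185.1 potential recoverers gives 228 v 333, 191 v 315 and 144 v 277 events for medians of 18, 24 and 36 h. The shares after 24 h stay at 32%, 39% and 48%.

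**6. Truncation or coarse timing?** A simulated log-rank test (assumed hazard ratio 1.35, 211 per arm, 600 runs, no deaths) separates the two:

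| Control median | Exact times to 72 h | Exact times to 24 h | Grouped at 12/24 h |
|---|---|---|---|
| 18 h | 84% | 67% | 67% |
| 24 h | 82% | 61% | 60% |
| 36 h | 81% | 52% | 53% |

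Grouping costs almost nothing. Stopping at 24 h costs about 17 to 28 percentage points.

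**The case against.** The strongest reply is that recovery will be seen anyway. Artesunate runs until the child is conscious, oral combination therapy starts on regaining consciousness, and time to full oral treatment is itself a secondary outcome with no 24 h limit. The timeline is a summary grid in an article, and the case record form is not shown. This stands as far as it goes: bedside staff must know when a child wakes. But the article does state an outcome definition and a schedule, and both stop at 24 h. Time to oral treatment is no substitute, because it also requires that the child tolerates it.

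A second reply is that the hypothesis concerns the first 24 h, so the 12 and 24 h counts are a deliberate choice, and that 48 h survival and day-29 neurological status cover lasting benefit. The counts are indeed deliverable as defined. That supports keeping them, but it does not reconcile them with a time objective.

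A reader might go further than the documents allow in three ways:

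- **That the time objective and its analysis cannot be delivered at all.** A grouped comparison censored at 24 h is possible.
- **That parasite clearance fails in the same way.** The row "Parasitaemia" also stops at 24 h, but the Kaplan-Meier/Cox sentence does not name it and its objective is a clearance rate.
- **That sustained defervescence can never be judged.** It can be for a child already below the threshold at 12 h.

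**Conclusion.** The mismatch is real and concerns secondary outcomes. The objective and the analysis call for recovery times; the outcome definitions and the schedule supply two readings and nothing after 24 h, although treatment is tied to consciousness beyond that point. The objective is only partly met.

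The size depends on how fast children wake, which the protocol does not state. For assumed control medians of 18 to 36 h and a hazard ratio of 1.3, roughly 32% to 48% of recoveries by 72 h fall after the last scheduled reading, with or without the allowance for deaths. The power figures are illustrative only. They rest on an assumed median, hazard ratio and exponential form, deaths lower the event counts, and the protocol claims no power for this endpoint.

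**What to change.** Preferred: in the Secondary outcomes and the Participant timeline, extend the coma score and axillary temperature to the existing 48 and 72 h columns, and to recovery if that is later. Record on the case record form the time at which sustained recovery of consciousness, and sustained defervescence, is first observed. Run the planned time-to-event analysis on those times with death before recovery as a competing event, because survival is the outcome on which the arms are expected to differ. Keep the 12 and 24 h proportions as they are.

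Alternative: if only the first 24 h is of interest, reword the objective and the Kaplan-Meier/Cox sentence so that consciousness and defervescence are compared as proportions at 12 and 24 h.

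The first option costs a table amendment and a few form fields, with no extra children and no new columns in the timeline. The 48 and 72 h columns already carry survival, electrocardiography and glucose, and consciousness must be followed to apply the treatment rules. The article describes the trial as active but not recruiting, so the change may still be possible before data are lost. No treatment rule needs to change.

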### Sample size {14}

The sample size for this study was calculated using the G*Power calculator, based on the reported outcomes of cerebral malaria with quinine monotherapy (23.0%) and a dual quinine and artesunate combination therapy (12.5%) [10, 18–20]. Going for a difference of 23.0 to 12.5%, a sample size of 470 participants is required accounting for a 10% attrition rate at 80% power of a 2-sided alpha level of significance of 0.05. Based on 1:1 allocation, the treatment arm will have 235 participants and the same number for the control arm. The details of the selected studies for the sample size calculation are shown in a supplementary document as a table.

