## Research problem

Severe malaria with multiple organ dysfunction is a major killer of children under-five in sub-Saharan Africa [1]. The morbidity and mortality rate of 35% with the current monotherapy is unacceptably high [8]. There is a need for modification of the current treatment regimen to improve outcomes and prevent the development of resistance, recrudescence and treatment failure.

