## Trial design {8}

This will be a triple blinded, parallel randomized controlled trial consisting of one treatment (experimental arm: intravenous artesunate + quinine) and one control arm (intravenous artesunate). Patient allocation will be in the ratio of 1:1. The assignment of patients into the study arms will be randomized.

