#### Explanation for the choice of comparators {6b}

Intravenous artesunate alone will be used as a comparator in this study. The choice of the two antimalaria is based on the difference in pharmacodynamics and varying mechanism of actions of the artemisinin derivatives compared with quinine. It is assumed that a synergistic action of the combined drugs against the erythrocytic and gametophyte stages of malaria parasite may enhance clearance. In addition, quinine is the only licenced alternative intravenous antimalaria by the WHO besides the artemisinin derivatives. These are the current standard treatments for cerebral malaria by the World Health Organization. In order to facilitate blinding, the monotherapy group (control) will also receive intravenous dextrose water or water for injection to maintain the similarity of treatment administration with the dual-therapy group (the treatment arm).

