### Outcomes {12}

#### The primary outcome

The primary outcome is survival measured at 48 h post-randomization.

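### The 80% power is calculated for quinine alone against quinine plus artesunate, but the trial compares artesunate alone with artesunate plus quinine

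*Protocol article*

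**What the plan says.** The section Sample size {14} of the protocol article states that the calculation is "based on the reported outcomes of cerebral malaria with quinine monotherapy (23.0%) and a dual quinine and artesunate combination therapy (12.5" per cent). It continues "Going for a difference of 23.0 to 12.5" per cent, and concludes that "a sample size of 470 participants is required accounting for a 10% attrition rate at 80% power of a 2-sided alpha level of significance of" (the alpha level given is 0.05). On the split: "Based on 1:1 allocation, the treatment arm will have 235 participants and the same number for the control arm".

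The comparator is defined differently. Trial design {8} describes "one treatment (experimental arm: intravenous artesunate + quinine) and one control arm (intravenous artesunate"). Explanation for the choice of comparators {6b} says "Intravenous artesunate alone will be used as a comparator in this study". The control-arm section and Sequence generation {16a} agree: control patients receive dextrose water where the experimental arm receives quinine. The Abstract also names artesunate only as the control.

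On the endpoint: "The primary outcome is survival measured at 48 h post-randomization".

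Two other background figures appear. Research problem says "The morbidity and mortality rate of 35% with the current monotherapy is unacceptably high", and the Abstract also gives 35%. Background and rationale {6a} gives current mortality from severe malaria as 22.5% to 34.7% across Africa and Asia.

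**The concern.** A power statement needs an event rate for the trial's own control arm and an effect for the treatment that the trial adds. Here both come from another contrast. Going from quinine alone to quinine plus artesunate shows what artesunate adds. In this trial every patient receives artesunate, and the question is what quinine adds. The first effect does not tell us the second, and mortality on quinine is not mortality on artesunate unless someone argues that it is.

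At stake is how the result will be read. A non-significant result from a trial described as having 80% power tends to be taken as evidence against the combination. That reading is safe only if the 80% belongs to the comparison made.

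**Working it through.** **Inputs, all from Sample size {14}:** p1 = 0.230, p2 = 0.125, two-sided alpha 0.05, power 0.80, 10% attrition, 1:1 allocation, total 470. The planned difference is 10.5 points and the planned risk ratio is 0.125/0.230 = 0.543.

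**Step 1. Reproduce the plan's figure.** The pooled two-proportion formula is

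n per arm = [1.96·√(2p̄(1−p̄)) + 0.8416·√(p1(1−p1) + p2(1−p2))]² / (p1−p2)²

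With p̄ = 0.1775, the first term is 1.96 × 0.5404 = 1.0591 and the second is 0.8416 × 0.5352 = 0.4505. So n = (1.5096)²/0.011025 = 206.7, that is 207 per arm and 414 in total. Dividing by 0.9 gives 460, within 3% of the stated 470.

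**Step 2. Power at the planned size.** 470 × 0.9 = 423 evaluable, or 211 per arm after rounding down. The formula is

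power = Φ{[|p1−p2|·√n − 1.96·√(2p̄(1−p̄))] / √(p1(1−p1) + p2(1−p2))}

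It gives Φ[(0.105 × 14.526 − 1.0591)/0.5352] = Φ(0.871) = 80.8%. Fisher's exact test at 211 per arm gives 77.9%. The arithmetic is sound for the inputs used.

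**Step 3. Recompute for the trial's own comparison.** The article states no artesunate-alone rate, so control mortality has to be varied as an assumption. The same formula with 211 per arm is applied under two readings of the planned effect: the risk ratio kept at 0.543, or the dual arm kept at 12.5%.

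| Assumed mortality on artesunate | Power, risk ratio 0.543 | Power, dual arm 12.5% |
|---|---|---|
| 35% | 96% | over 99% |
| 25% | 85% | 91% |
| 23.0% (the quinine figure) | 81% | 81% |
| 22.5% | 80% | 77% |
| 20% | 74% | 55% |
| 18% | 69% | 35% |
| 15% | about 60% (59.5%) | 11% |
| 12% | 49% | not applicable (dual rate above control) |

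Worked example, 20% against 12.5%: p̄ = 0.1625, and Φ[(0.075 × 14.526 − 1.96 × 0.5217)/0.5190] = Φ(0.129) = 55%.

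**Step 4. What 470 can detect.** Solving the same formula for 80% power: a control rate of 35% needs a dual rate of 22.7% (risk ratio 0.65), 25% needs 14.2% (0.57), and 15% needs 6.6% (0.44).

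**Step 5. Dependence on the effect scale.** If the 10.5-point absolute difference is held instead, power moves the other way: 66% at a control rate of 35% and 86% at 20%. So the control rate and the effect expected from quinine must both be stated before any power figure has meaning.

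**The case against.** The strongest reply is that 23.0% may be a workable control rate whatever its label. Background and rationale {6a} gives 22.5% as the lower end of current severe-malaria mortality, in a paragraph that calls current treatment monotherapy. At 22.5% the power is 80% with the risk ratio held and 77% with the dual rate held. No mortality figure in the article is lower except the 12.5% for dual therapy. This stands as a reason not to call the trial underpowered. It does not supply the missing link: that figure is for severe rather than cerebral malaria, names no drug and has no time point.

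A second reply is that the supplementary table of source studies, which is not at hand, may contain an artesunate rate, or that quinine is a slip for artesunate. Either is possible. The current text still names quinine as the source of the 23.0%, so it needs correcting in either case. The missing time point for the 23.0% and 12.5% is different: the table may well give it, so its absence is not counted as an error here.

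Three stronger readings are tempting and are not supported:

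- A reader might infer that the trial is underpowered. The documents cannot show this. Control rates below 22.5% have no source in them, and at 25% or 35% power exceeds 80% under both readings in the table.
- A reader might infer that 80% holds only if artesunate mortality equals the quinine figure. That is false. At 35% control mortality a risk ratio of 0.65 is enough.
- A reader might take the 35% as contradicting the 23.0%. It is a combined morbidity and mortality figure with no drug named, not a control-arm assumption. It needs relating to the planning rate, but no contradiction is demonstrated.

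**Conclusion.** Wrong as written. The sample size justification describes a contrast that the trial does not make, and nothing in the article connects the two. The number 470 is not miscalculated. What fails is the claim that it gives 80% power for artesunate against artesunate plus quinine.

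Over assumed control rates of 15% to 35%, power at the planned size runs from about 60% to 96% with the planned risk ratio, and from 11% to over 99% with the dual arm at 12.5%. These ranges rest on 211 evaluable patients per arm, the pooled two-proportion formula and artesunate rates that the documents do not supply. They show how much the power depends on the missing input, not which way the error runs.

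**What to change.** In Sample size {14}:

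1. Replace the 23.0% with a sourced mortality for cerebral malaria on intravenous artesunate at the 48 h primary endpoint, or justify 23.0% as a stand-in for it.
2. State the added effect expected from quinine, and on which scale.
3. Say how the chosen rate relates to the 22.5% to 34.7% in Background and rationale {6a} and to the 35% in the Abstract and Research problem.
4. Replace the unqualified 80% with a table of power, or detectable difference, for 470 patients under artesunate against artesunate plus quinine. Run it over control rates from about 12% to 35%, with rates below 22.5% labelled as assumptions. A table stopping at 25% would leave out the article's own higher figures and tilt the picture downward.

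Cost: some rewriting, and a power figure that may become less favourable. The change itself adds no patients. Trial status says the trial is not recruiting, so the restatement can be made before the first patient is enrolled.
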